#### **7.2.6 Processing of Dropout or Missing Values**

The most recent data will be used for data analysis as if it was obtained at the corresponding point in time(Last Observation Carried Forward Method) should the subject is disqualified due to dropout or there is a missing value in data during FAS analysis before the clinical trial ends.

#### **7.2.7 Scheduled Intermediary Analysis and Data Monitoring**

Intermediary analysis and establishment of data monitoring committee were not planned for this clinical trial.

## **8. ADVERSE EVENTS**

### **8.1 Definition of Adverse Events**

#### **(1) Adverse Events (AE)**

It includes all harmful and unintended signs (Includes signs and anomalies in test results), symptoms, or diseases that occur in subjects administered with clinical trial drugs and it does not require a cause-and-effect relationship with the investigational product. Adverse events include but not limited to the following.

- Abnormal test results
- Clinically significant symptoms or signs
- Change in results of physical examinations
- Hypersensitivity
- Progression/Aggravation of existing disease

#### **(2) Adverse Drug Reaction (ADR)**

It refers to all harmful and unintended reactions in random dosages of investigational products where cause-and-effect relationship with investigational products cannot be denied.

#### **(3) Unexpected Adverse Drug Reaction**

It refers to difference in positive testing or hazard level of adverse drug reaction based on the drug substance related information provided through clinical trial data, attachment documents for drug substance, etc.

#### **(4) Serious AE/ADR**

It refers to one of the following among adverse events or adverse drug reactions occurring in random dosages of investigational products.

- ① When there is a death or danger of life

- ② When there is a need for hospitalization or extension of hospitalization period
- ③ When it causes a permanent or severe disability/performance decrease
- ⑤ When there is a malformation or anomaly in the embryo
- ⑥ Other medically serious circumstances

Even if it is not an event listed above but when an event that is considered to have significant impact on the well-being and health of patient by medical opinion occurs, determine whether it is considered as a serious adverse event through assigned physician and relevant experts and take appropriate action.

## **8.2 Collection and Record of Adverse Events**

- Records of adverse events should be collected from after administration of investigational product until the final visit. All medical cases occurring prior to administration of investigational product shall be recorded as current medical history.
- Records of serious adverse events are collected after consent for participation in clinical trial is given and such events are all recorded as serious adverse events even if they occur prior to administration of investigational product.
- Adverse events should be reported including the name, sustained period (Starting date/Disappearance date), severity, cause-and-effect relationship with investigational product, relevant actions, results, remedial treatment, and serious adverse events.
- Investigator should utilize standard medical terms to use name of overall diagnosis or symptom rather than recording each symptom or sign when recording the adverse event.
- Adverse events occurring during clinical trial should be tracked until the adverse event disappears or turns in stable results or until follow-up survey in subject fails.
- Only adverse events that are serious and related to investigational product should be reported for adverse events occurring after conclusion of clinical trial.

## **8.3 Assessment of Adverse Events**

### **8.3.1 Assessment of Severity**

Severity of each adverse event and serious adverse reaction is assessed as below.

|                    |                                                        |
|--------------------|--------------------------------------------------------|
| Grade 1 (Mild)     | : Easily withstandable adverse event                   |
| Grade 2 (Moderate) | : Adverse event that disrupts daily life significantly |
| Grade 3 (Severe)   | : Adverse event that makes daily life impossible       |

Definition of activities of daily life(ADL) is as below.

- All activities which occur throughout daily life to manage one's body  
(Ex: Shower, dressing/undressing, eating, medicating, personal hygiene, personal care)

Adverse event or serious adverse reaction can all be assessed to be severe according to definition above but not all severe adverse events are serious adverse reactions.

### **8.3.2 Assessment of Cause and Effect Relationship**

Relevance to investigational products for adverse events shall be assessed by the investigator by categories below.

#### **① Definitely Related**

- When there is evidence of this drug being administered
- When the administration of this drug is the most probable reason compared to other causes for the adverse effect
- When the adverse event disappears after stopping administration
- When re-administration(Rechallenge, perform only when possible) results test positive
- When the adverse effect is exhibiting symptoms consistent with information already known for this drug or drug of same group

#### **② Probably Related**

- When there is evidence of this drug being administered
- When chronological sequence of incidence and administration of this drug are logical
- When the administration of this drug is a more probable reason compared

- to other causes for the adverse effect
- When the adverse event disappears after stopping administration

**③ Possibly Related**

- When there is evidence of this drug being administered
- When chronological sequence of incidence and administration of this drug are logical
- When the administration of this drug is about the same in terms of probability compared to other causes for the adverse effect
- When the adverse event disappears after stopping administration(When executed)

**④ Probably Not Related**

- When there is evidence of this drug being administered
- When there is another more probable cause for the adverse effect
- When results after stopping administration are negative or ambiguous (When executed)
- When the adverse event continues but ambiguous after stopping the administration of investigational product

-

**⑤ Definitely Not Related**

- When there is no evidence of this drug being administered
- When there is another highly probable reason for the adverse event
- When the adverse event does not disappear after stopping the administration of investigational product

**⑥ Unknown**

**8.4 Report of Serious Adverse Events**

All serious adverse events during clinical trial period must be reported via phone/fax to the client within 24 hours of acknowledgement by the investigator regardless of relevance to investigational product or its administration. Only serious adverse events related to investigational product shall be reported for adverse events that occur from the final investigational product administration until the 7th day after final administration.

In order to protect confidentiality of personal information of subjects when reporting serious adverse events to the client, the investigator must utilize subject identification codes instead of personal information of subjects such as their names, resident registration number, and address. All personal information aside from the identification code shall be redacted as necessary even when some copies of medical records are required.

Also, the investigator must perform a follow-up report if additional information regarding the serious adverse event has been acquired. The investigator must report regularly until the corresponding serious adverse event is concluded (Disappearance of corresponding adverse drug reaction or until follow-up report becomes impossible).

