### **8.6 Pregnancy**

Pregnancy during clinical trial period is not considered as an adverse event and selective abortion (Abortion for treatment is not included) without complications or hospitalization for normal childbirth are also not considered as adverse events.

However, if a subject becomes pregnant during the clinical trial period (After administration of investigational product ~ Within 28 days of final administration), the subject shall be dropped from the clinical trial immediately and it shall be reported through the pregnancy report form within 24 hours of pregnancy discovery to the client. Investigator must perform follow-up report until childbirth for both the pregnant woman and the child even if the subject

stops participating in the clinical trial or after conclusion of clinical trial.

Severe complications of birthmother, natural miscarriage, ectopic pregnancy, stillbirth, death of newborn child, congenital malformation, and other events are considered to be severe adverse events and the investigator must report them accordingly.

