- (15)Skin reaction: This drug may cause serious adverse skin reaction such as deciduous dermatitis, Stevens-Johnson syndrome, and toxic epidermal necrolysis and they may be fatal. Such serious adverse reactions may occur without warning symptoms. Most of the time, such reactions occur within 1 month of initial administration. Patients should be aware of serious skin symptoms and signs and stop administration of this drug when skin rashes or other initial symptoms and signs of hypersensitivity occur.

- (16)Some asthma patients may be sensitive to aspirin. Use of aspirin for aspirin sensitive asthma patient may be result in severe bronchospasm

which may be fatal. Cross-reaction including bronchospasm between aspirin and other non-steroid anti-inflammatory pain relievers in such aspirin sensitive patients has been reported. Therefore, this drug should not be administered to such aspirin sensitive patients and be administered with caution for asthma patients.

- (17) This drug cannot substitute corticoid agents or be used as a drug for treating corticoid deficiency. Sudden stoppage in corticosteroid administration may cause aggravation of corticosteroid-responsive disease. Administration of this drug for a patient administered with corticosteroid long term requires gradual reduction of dosage.
- (18) Patients experiencing other central nervous disorders including drowsiness, dizziness, and visual impairment should avoid driving or handling machinery.

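### Sections 8.2 and 8.4 give conflicting rules for reporting serious adverse events after the last dose

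*Protocol*

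**What the plan says.** Three sections of the protocol bear on which serious events a site must record and report.

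- **Section 8.2, start and end of collection.** For adverse events in general: "Records of adverse events should be collected from after administration of investigational product until the final visit". For serious events the start is earlier: "Records of serious adverse events are collected after consent for participation in clinical trial is given".
- **Section 8.2, after the trial.** "Only adverse events that are serious and related to investigational product should be reported for adverse events occurring after conclusion of clinical trial". No end date is given.
- **Section 8.4, first sentence.** "All serious adverse events during clinical trial period must be reported via phone/fax to the client within 24 hours", and this holds regardless of relatedness.
- **Section 8.4, second sentence.** The duty narrows to serious events with a link to the study product, and the window is worded as "adverse events that occur from the final investigational product administration until the 7th day after final administration". Nothing is said about what applies after day 7.
- **Section 8.6, on pregnancy.** The clinical trial period is glossed as "After administration of investigational product ~ Within 28 days of final administration".

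**The concern.** Section 8.2 changes from all serious events to related ones at the end of the trial. Section 8.4 makes the same change at the last dose. These are different anchors, and the two sections also end differently: 8.2 has no end, while 8.4 names only day 7. The term on which the first sentence of 8.4 depends, the clinical trial period, is not defined there, and 8.6 gives it a third end point.

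Two sites that each follow the text literally could report different events. The report from site to sponsor within 24 hours is an important safety channel in this trial. Section 7.2.7 plans no data monitoring committee, and under Section 8.5 suspected unexpected serious reactions reach the regulator through the sponsor. A late related serious event that a site believes to be outside its reporting window might not reach the sponsor.

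**Working it through.** No figure of the plan has to be reproduced here; the check sets the rules side by side. Let L be the day of the last dose, V the day of the final visit (V on or after L), and t the day on which a serious event starts.

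| Onset and causality | Section 8.2 | 8.4, first sentence | 8.4, second sentence |
|---|---|---|---|
| After L, up to V and within L + 7, unrelated | Collected | Reportable | Excluded |
| After L + 7, up to V, unrelated | Collected | Reportable | Silent |
| After V, within L + 7, related | Reportable | Depends on the meaning of the trial period | Reportable |
| After V and after L + 7, related | Reportable, no end | Depends on the meaning of the trial period | Outside the window |

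The table treats the days up to V as inside the clinical trial period.

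**Conflict (a): before the final visit (row 1).** Its length is V − L, up to the 7 days that the second sentence of 8.4 covers.
- For a subject who completes treatment this is close to zero. Section 4.2.4 places Visit 4 on the last day of the study, and Section 6.6 counts scheduled doses up to the morning of the next visit.
- For a subject who stops early it depends on how soon the last visit takes place. Section 4.2.4 has the Visit 4 items done at a premature end, and Section 5.3 asks for a last visit, but neither sets a number of days.
- Illustration, assuming a last dose on Day 14 and a last visit only on Day 28: V − L = 28 − 14 = 14 days. Up to Day 14 + 7 = 21 an unrelated serious event is both required and excluded within 8.4. From Day 22 to Day 28 the second sentence is silent.

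**Conflict (b): after day 7 (row 4).** For t later than both V and L + 7, a related serious event is reportable without limit under 8.2 and lies outside the only post-dose window in 8.4. This does not depend on stopping early. With a last dose on Day 28, the 8.4 window closes on Day 28 + 7 = 35, and a related serious event on Day 36 is treated differently by the two sections.

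**The third end point.** If the gloss in 8.6 were carried over to 8.4, the first sentence would cover all serious events, whatever the cause, to L + 28. That is 28 − 7 = 21 days beyond the day-7 limit in the second sentence, and the two sentences would then disagree for every subject in the first 7 days after the last dose. The overview table uses the same label for the study calendar (12 months from IRB approval), so it supplies no end point for an individual subject.

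**The case against.** The strongest reply is that the text can be read as one workable scheme. The last dose and the end of participation are meant to nearly coincide, so the second sentence of 8.4 can be taken as the tail after the trial, with the same restriction to related events as 8.2. A related serious event stays reportable under 8.2 whatever 8.4 says. Events already open when a subject stops are tracked until they resolve or stabilise (8.2), are followed up at dropout (5.3), and if serious are reported repeatedly (8.4).

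Much of this stands. Conflict (a) is small for completers, only events with new onset after stopping are at issue, and a late related event goes unreported only where a site applies 8.4 alone. The reply does not remove the mismatch. Section 8.4 counts from the last dose and not from the final visit, it stops at day 7 where 8.2 does not stop, and nothing says which section prevails.

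A reader might go further and infer that subjects who stop early are left uncovered within a one-month risk period. The general cautions for both drugs (Appendix 11.1.1 and 11.1.2) say of serious skin reactions: "Most of the time, such reactions occur within 1 month of initial administration". The day count is correct as far as it goes. With a last dose on Day 14 the 8.4 window closes on Day 21, while a month of 28 to 31 days from Day 1 ends on Day 29 to 32, which is 8 to 11 days later. The inference still fails. The sentence is product information about most cases, and it gives no risk period for someone who has stopped the drug. A related skin reaction in those days remains reportable under 8.2. On the 8.6 reading, the first sentence of 8.4 would also cover it, to Day 14 + 28 = 42.

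**Conclusion.** The contradiction is real and can be read directly from the text. Unrelated serious events between the last dose and the final visit are both required and excluded. Related serious events from day 8 after the last dose are reportable under 8.2 and outside the stated window of 8.4. The practical risk is conditional: if a site follows 8.4 alone, a late related serious event, such as a skin reaction starting after an early stop, may go unreported. It is worth correcting because the correction is cheap and concerns safety capture.

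The documents support no number of affected subjects or events. A reader might take 10% of 190, that is 19 subjects, but the 10% in Section 3.2.2 is an allowance for loss to follow-up in the sample size. It does not count subjects who stop before any given day. A reader might also infer a biased safety comparison between arms. That would need differential discontinuation and enough late events to matter, and the documents show neither; Section 7.2.5.1 moreover compares reactions reported during the trial period.

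The verdict assumes that the final visit ends a subject's participation, and that the 28-day gloss in 8.6 was written for pregnancy reporting. If that gloss is meant to hold throughout, the inconsistency is larger.

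**What to change.** Reconcile 8.2, 8.4 and the meaning of the clinical trial period in 8.6 into one rule with one anchor, and use the same words in 8.2 and 8.4:

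- From consent to the final visit, report all serious events regardless of causality.
- Start the restriction to related events only after the final visit, not at the last dose.
- Give that later period the same end in both sections, or no end, as 8.2 now says.
- Define the clinical trial period once for the individual subject. If 28 days after the last dose is meant for pregnancy alone, say so in 8.6.

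No additional safety call is needed for this. The telephone monitoring in Section 5.4 serves compliance with visits, administration and examinations, so a call at one month would be a new procedure.

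The cost is amended wording and possibly a few more reports of unrelated serious events. No visit, assessment or sample size changes.

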#### **8.5 Report of Suspected Unexpected Serious Adverse Reaction(SUSAR) and Countermeasure**

Clinical trial supervisor must determine continuance or stoppage of clinical trial by reporting to the institutional review board(IRB) upon occurrence of suspected unexpected serious adverse reaction(SUSAR) during clinical trial period and report to the Director of KFDA through the client within designated periods as listed below. Refer to the KFDA Clinical Trial Adverse Event Reporting Guidelines for further details.

- ① SUSAR which causes death or threatens life must be reported as quickly as possible to the Director of KFDA via phone/fax/document within 7 days from initial reporting date by the client and a complete report within 15 days of initial discovery is also required.
- ② All other SUSARs must be reported as quickly as possible within 15 days after client has been reported or notified.

Obligations of each party upon occurrence of “Suspected Unexpected Serious Adverse Reaction(SUSAR)” are as below. Clinical trial supervisor and instructor must focus on safety of subjects and take appropriate actions quickly upon occurrence of SUSAR to minimize the adverse reaction.

##### **(1) Obligations of Clinical Trial Supervisor**

Clinical trial supervisor must report any serious adverse drug reaction during clinical trial to the clinical trial review committee and client and stop the clinical trial for corresponding investigational product partially or entirely until further instructions.

#### (2) Obligations of Clinical Trial Instructor

Clinical trial instructor must report any critical adverse drug reaction during clinical trial to the clinical trial supervisor and client immediately.

#### (3) Obligations of Institutional Review Board

The institutional review board must take necessary actions such as order for stoppage for part or entire clinical trial should serious adverse drug reaction is observed through clinical trial supervisor.

#### (4) Obligations of Client

The client must submit the copy of report submitted by the clinical trial supervisor or clinical trial instructor regarding SUSAR to the Director of KFDA immediately and quickly notify the corresponding institutions should multiple institutions are performing the clinical trial.

### **8.6 Pregnancy**

Pregnancy during clinical trial period is not considered as an adverse event and selective abortion (Abortion for treatment is not included) without complications or hospitalization for normal childbirth are also not considered as adverse events.

However, if a subject becomes pregnant during the clinical trial period (After administration of investigational product ~ Within 28 days of final administration), the subject shall be dropped from the clinical trial immediately and it shall be reported through the pregnancy report form within 24 hours of pregnancy discovery to the client. Investigator must perform follow-up report until childbirth for both the pregnant woman and the child even if the subject

stops participating in the clinical trial or after conclusion of clinical trial.

Severe complications of birthmother, natural miscarriage, ectopic pregnancy, stillbirth, death of newborn child, congenital malformation, and other events are considered to be severe adverse events and the investigator must report them accordingly.

## **9. ETHICS AND ADMINISTRATIVE PROCEDURE**

### **9.1 Clinical Trial Plan Compliance**

The investigator must conduct the clinical trial in compliance with the clinical trial plan. The clinical trial cannot be altered from the clinical trial plan unless elimination of immediate risk factors for the subject is necessary and any violations must be recorded with its details and grounds. Even if the investigator determines that the violation of the test plan can improve the performance of clinical trial, the investigator shall not execute the change until agreement from the client and the approval from the IRB(Includes the Director of KFDA if necessary) for the change are given.

### **9.2 Authorization and Revision of Clinical Trial Plan**

When seeking authorization of clinical trial or revised clinical trial, authorization from the Institutional Review Board(IRB) is required for clinical trial plans and revised plans by stage as well as authorization from the Director of KFDA if necessary. Subjects cannot participate in the clinical trial prior to authorization.

### **9.3 Subject Consent Procedure**

Subject description and consent forms can only be used after authorization from the Institutional Review Board(IRB). Consent from subject must be given according to ethics and pharmaceutical clinical trial management standards based on the Declaration of Helsinki. The investigator must describe the clinical trial to the subject(or the representative of the subject) prior to proceeding with all clinical trial related procedures and receive written consent from the subject. The investigator must store the original copy of signed consent form in the investigator files and provide the copy of written consent form along with description form explained to the subject(or the representative of the subject). Consent procedure for the patient must be recorded on the evidentiary materials.

When it is impossible for the subject to give consent, consent must be given through the representative of the subject. If neither the subject nor the representative of the subject is literate, an observer must be present for all procedures of giving consent. The subject or the subject's representative should sign the consent form if possible after agreeing to participating in the

clinical trial and the observer must sign on the consent form to prove that the information above was described and understood accurately.

If the subject description and consent forms are revised, they must be reapproved by the IRB and consent must be given by the subject(or the representative of the subject) already undergoing clinical procedure once again. The investigator at this time shall record the subject, date, and details of announcement on the evidentiary materials.

Also, vulnerable subjects(Ex: Hospital employees, school students, etc.) according to the opinion of IRB within testing institution may also be recruited and the clinical trial supervisor and instructor must comply with the following protective measures and plans along with the obligations as a investigator when registering 'Vulnerable subjects'. Recruitment of vulnerable subjects without approval from IRB of the testing institution cannot be registered.

[Protective measure and policy when registering 'Vulnerable subjects']

- 1) This clinical trial shall recruit employees within the hospital only through the method of posting a poster containing recruitment notice authorized by IRB in locations permitted by the hospital and employees that are directly related to the investigator in terms of chain of command shall not be recruited.
- 2) If the hospital employee wishes to participate through recruitment by posters within the hospital, sufficient description and time for consent procedure must be given according to KGCP and consent must be given according to the opinion of IRB in the corresponding institution through even more detailed description on importance of voluntary participation.
- 3) Subjects must be notified of contact information for IRB in order for them to independently discuss ethical issues or their rights regarding the clinical trial.

[Obligations of investigator when registering 'Vulnerable subjects']

- 1) Subjects should be able to freely and voluntarily decide on participation of clinical trial.
- 2) Clinical trial participation shall not be coerced in any form.
- 3) A subject can withdraw participation in clinical trial at any time.
- 4) There shall be no disadvantage related to participation of clinical trial.
- 5) Appropriate compensation as listed in the consent description form shall be

given like other subjects upon voluntary participation.

6) Employees directly related in chain of command shall not be recruited.

Subject consent description and written consent forms for this clinical trial can be found under Clinical Trial Plan Attachment 1.

